**Summary of Study Protocol**

| **Project Name** | A study protocol of the rehabilitative efficacy of cardiovascular ultrasound therapy after percutaneous coronary intervention in patients with coronary artery disease: A multicenter, parallel-group, randomized controlled study |
| --- | --- |
| **Objective** | The aim of this study is intended to evaluate the rehabilitative efficacy of cardiovascular ultrasound therapy in patients with coronary artery disease (CAD) who had already undergone percutaneous coronary intervention (PCI). Specifically, the study aims to examine the effects of cardiovascular ultrasound therapy on inflammatory markers, serum lipids, endothelial function, cardiac function, carotid artery plaque, and hemodynamics. In addition, the study will analyze patients’ heart rate variability (HRV), record their symptoms, and score depression and anxiety. |
| **Research Hypothesis** | Cardiovascular ultrasound therapy has the potential to reduce perioperative myocardial damage, reduce the production of inflammatory factors and inflammatory cells, and has a certain regulatory effect on blood lipids, platelet function, hemodynamics and blood pressure in patients after PCI. |
| **Study Design** | This study is a multicenter, parallel-group, randomized controlled clinical trial. Subjects were enrolled by randomization into groups of 20 per center, with 10 in the control group and 10 in the treatment group. Each participating unit completes the relevant content of the subject case list. |

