**3.2.2 Exclusion Criteria:**

• ST-segment elevation myocardial infarction and non–ST-segment elevation myocardial infarction;

• Occlusion of branch vessels during PCI;

• Perioperative use of hormones or immunosuppressants;

• Combined infection or other inflammatory diseases;

• Postoperative fever;

• Allergy to contrast media or cardiovascular ultrasound acoustic head–related materials;

• Changes in lipid-lowering, antiplatelet, and antihypertensive drug regimens during treatment;

• A clear diagnosis of autoimmune disease;

• A history of other surgeries or trauma in the preceding 7 days;

• Infection with the novel coronavirus during the preceding month;

• Previous PCI treatment;

• Previous cardiovascular ultrasound treatment;

• Diabetes mellitus.

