**3.3.2 Withdrawal/drop-off as determined by the investigator**

The withdrawal decided by the investigator refers to the fact that the enrolled subjects are not suitable to continue the trial during the trial, and the investigator decides to withdraw from the trial.

1) During the trial, there are changes in the subject's condition, such as acute stent thrombosis, malignant arrhythmia, contrast nephropathy, acute left heart failure, hemodynamic instability, etc., which affect the compliance of continuing to participate in the trial or continue to participate in the trial may affect the safety of the subject, and the investigator believes that the patient should withdraw;

2) Patients with a definite diagnosis of PCI-related myocardial infarction at 48h;

3) Subjects who violate the inclusion/exclusion criteria, or have poor protocol compliance.

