**3.5 Randomization and blinding**

Using a randomized 1:1 ratio, participants will be allocated into either of two groups: the cardiovascular ultrasound therapy group and the control group. This process will be facilitated by a computer-generated randomization sequence. To uphold the integrity of the allocation process, a team of research assistants not involved in clinical care or outcome assessment will meticulously craft sequentially numbered, opaque, sealed envelopes based on the predefined randomization list. This meticulous approach will ensure the safeguarding of confidentiality and the autonomy of allocation data. When appropriate, the assistants will open envelopes and ensure the coordination of therapeutic interventions.

Given the distinctive visual and operational characteristics of cardiovascular ultrasound therapy, the assignment results will not be concealed from the attending physicians or the patients. Only the investigative team members responsible for the collection of primary outcome data will remain masked. Consequently, the study design adheres to the framework of a nonblinded controlled trial. Patients will retain the prerogative to decline study participation, in which case they would receive standard care only.

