**3.7.2 Intervention description**

Participants allocated to the intervention group will undergo a 10-day regimen utilizing a medical cardiovascular ultrasound therapy device (838C-M-L-I/II, Shenzhen, China). The ultrasound instrument is equipped with a sound head comprising five transducer units operating at an ultrasonic frequency of 0.84 MHz with a sound intensity range of 1 W/cm^2^–1.25 W/cm^2^. The therapeutic ultrasound sessions require a controlled environmental temperature. Patients will assume the supine position, exposing the precordial region, with the 5-pronged head positioned parallel to the heart’s long axis; it should cover the entire precordial region including the right and left coronary arterial trunks and the aortic root (Fig.1). The five transducer units function sequentially in a scanning pattern, with each unit operating for 5 seconds and transitioning with a 0.5-second interval, following a clockwise rotation until the treatment has been completed. The cardiovascular ultrasound therapy device operates in a pulsed mode, and each treatment session lasts for 20 minutes; there would be two daily sessions for a total of 20 treatments. The control group was not given extracorporeal cardiac ultrasound therapy. Participants in the control group will not receive cardiovascular ultrasound therapy. cardiovascular ultrasound therapy will be assessed at baseline (24th-hour post-PCI), on the 10th day, and at the end of the first and third months post-intervention. If it is necessary to change the medication regimen as much as possible, if it is necessary to change the medication regimen, it should be decided after evaluation by the investigator, and if the medication regimen that does need to be changed has an impact on the test results, the patient should be excluded and the reasons for changing the medication regimen should be recorded in detail.

[figure not shown]

Fig. 1. Diagram of ultrasound head placement.

A: Patients undergoing cardiovascular ultrasound therapy. B is used in patients with occlusion of one coronary artery and C is used in patients with occlusion of both coronary arteries.

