**4** **Statistical analysis**

The baseline characteristics of both groups will be summarized using appropriate descriptive statistics. Analysis of both primary and secondary outcomes will be based on the intention-to-treat approach, ensuring that all participants remain assigned to their original group throughout the study.

Normally distributed data will be presented as the mean (standard deviation), and non–normally distributed data will be depicted as the median (interquartile range). Group comparisons will be conducted using independent sample tests, and within-group comparisons before and after treatment will be evaluated using paired sample tests. Clinical symptom variables will be portrayed as percentages. Categorical data will be assessed using either the chi-squared test or Fisher’s exact test. A significance level of.05 will be employed to interpret the P values. The statistical analysis will be conducted utilizing SPSS version 26 statistical software (IBM, Armonk, NY).

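### Two different rules remove randomised patients for drug changes during the trial; neither is reconciled with the intention-to-treat analysis, and neither prevents removal by staff who know the arm

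*Protocol*

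**What the plan says.** Five parts of the protocol bear on this point.

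- **Section 3.2.2**, repeated in the Subject population row of the Summary, lists as an exclusion criterion "Changes in lipid-lowering, antiplatelet, and antihypertensive drug regimens during treatment".
- **Section 3.3.2** gives as a ground for investigator-decided withdrawal of enrolled patients: "Subjects who violate the inclusion/exclusion criteria, or have poor protocol compliance".
- **Section 3.7.2** treats medication changes separately. Of a necessary change it says "it should be decided after evaluation by the investigator", and then "if the medication regimen that does need to be changed has an impact on the test results, the patient should be excluded", with the reasons to be recorded.
- **Section 3.5** states that "the assignment results will not be concealed from the attending physicians or the patients", and adds: "Only the investigative team members responsible for the collection of primary outcome data will remain masked".
- **Section 4** states: "Analysis of both primary and secondary outcomes will be based on the intention-to-treat approach".

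The Research Hypothesis in the Summary is also relevant. It proposes that ultrasound "has a certain regulatory effect on blood lipids, platelet function, hemodynamics and blood pressure in patients after PCI".

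**The concern.** A drug change during treatment cannot be known at enrolment, so it cannot work as an eligibility criterion. In practice it removes patients after randomisation, and section 3.3.2 supplies the route.

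The section 3.7.2 rule differs in scope and in trigger. Its trigger, an effect on the test results, is undefined and left to judgement. Two sites could treat the same patient in opposite ways and both be following the protocol.

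What is at stake is the set of patients behind the day-10 hsCRP and interleukin-6 comparison, and behind the lipid and haemodynamic secondary outcomes. The three named drug classes act on the things the hypothesis expects ultrasound to alter. The need for a drug change may therefore depend on the arm. If removal depends on both arm and outcome, the comparison is no longer protected by randomisation.

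**Working it through.** **1. The rules side by side**

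| | Section 3.2.2 with 3.3.2 | Section 3.7.2 |
|---|---|---|
| Drugs covered | Lipid-lowering, antiplatelet, antihypertensive | Medication regimen in general |
| Trigger | Any change | A needed change that affects test results |
| Window | During treatment | None stated |
| Criterion for impact | Not applicable | None stated |
| Masked decision | Not stated | Not stated |
| Retained in follow-up or analysis | Not stated | Not stated |

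A patient whose antihypertensive is changed on day 4, with no judged effect on results, is excluded under the first rule and kept under the second. A patient whose change in some other drug is judged to affect results is kept under the first and excluded under the second. Section 4 keeps both patients.

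**2. The plan's own figures**

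Section 3.4 gives 160 evaluable patients and 20% dropout: 160 / (1 − 0.20) = 200, or 100 per group. This reproduces. The step before it cannot be checked because no SD is stated. The SD implied by 4 mg/L, 80 per group, 90% power and two-sided 0.05 is

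SD = 4 / [(1.960 + 1.282) × √(2/80)] = 4 / 0.5125 ≈ 7.8 mg/L.

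**3. Illustration of what selective removal could do**

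Assumptions, none of them from the protocol: SD 7.8 mg/L, 100 per arm, no true effect, and the highest hsCRP values removed from one arm only. For normal data, removing the top fraction q lowers that arm's mean by about SD × φ(c) / (1 − q), where c is the upper-q normal quantile and φ the standard normal density:

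- q = 2%: 7.8 × 0.0484 / 0.98 ≈ 0.39 mg/L
- q = 5%: 7.8 × 0.1031 / 0.95 ≈ 0.85 mg/L
- q = 10%: 7.8 × 0.1755 / 0.90 ≈ 1.52 mg/L

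Simulation followed by a two-sample t-test gives the ranges below. The low end is normal data; the high end is lognormal data with an assumed mean of 10 mg/L.

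| Removed from one arm | Shift in difference | False-positive rate (nominal 5%) |
|---|---|---|
| 2% | 0.4-0.6 mg/L | about 7-10% |
| 5% | 0.8-1.2 mg/L | about 13-24% |
| 10% | 1.4-1.9 mg/L | about 28-55% |

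The sign depends on the arm. Removal from the ultrasound arm favours ultrasound; removal from control gives the same size against it. If the top 10% is removed from both arms the mean shift is zero. All these removal rates fit within the 20% dropout allowance, so losses on this scale would not stand out.

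**The case against.** **Impact need not mean the patient's own result.** The section 3.7.2 sentence is garbled, and it can be read as concerning drugs known to affect the assays, judged by drug type. That is fair. A reader might infer that the protocol tells investigators to exclude by outcome; the text does not say so. It sets no criterion, so removal guided by results is not prevented. Even the benign reading is a discretionary exclusion after randomisation.

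**The deciding investigator is not stated to be unmasked.** Correct. It is an inference from section 3.5, where masking is limited to those collecting primary outcome data.

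**Exclusion is not tied to an analysis set.** Also correct, and a statistical analysis plan may define the sets. A reader might conclude that the intention-to-treat analysis is abandoned; the supported statement is that the exclusions are not reconciled with it. Nothing keeps these patients in follow-up, however, and an analysis plan cannot recover day-10 samples that were never taken.

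**Section 4.3 plans extreme missing-data scenarios and a tipping-point style check.** These bear on absent values and would give some protection. They do not mention drug-change exclusions or retain the patients, and the imputation trigger is exclusion for missing data.

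**The direction is not known.** This stands. A reader might infer that the rules favour ultrasound. If ultrasound does improve lipids or blood pressure, drug changes could fall on ultrasound responders or on controls doing badly, and removing those patients could work against it.

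**Conclusion.** The point holds as an unreconciled conflict. The Summary and sections 3.2.2, 3.3.2 and 3.7.2 give two different grounds for removing randomised patients, and both clash with section 4. Sections 3.5 and 3.7.2 together leave removal by staff who know the arm, including removal guided by results, unprevented.

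Any resulting bias has unknown size and direction. The protocol gives no drug-change rate and no SD, so the figures above illustrate sensitivity and do not predict a result. Removal of 2% matters little (about 7-10% false positives). One-sided removal of the highest 10% is a worst case and should be quoted only as such.

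The change is still needed, because the conflict decides who is counted in the primary comparison and sites will act on the protocol wording.

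**What to change.** Reconcile the Summary and sections 3.2.2, 3.3.2 and 3.7.2 with section 4:

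1. **Summary and 3.2.2:** delete the drug-change criterion, or limit it to changes before randomisation.
2. **3.7.2:** replace the exclusion with a statement that all randomised patients remain in follow-up and in the intention-to-treat analysis whatever drug changes occur. Record each change by date, class and reason in both arms, and tabulate by arm.
3. **3.3.2:** state that withdrawal from treatment does not remove a patient from outcome collection, where consent allows, or from the analysis. Align 3.3.1, which counts stopping treatment as withdrawal.
4. **Section 4:** add one sensitivity analysis omitting patients with a change in the three classes between randomisation and day 10. Define it by class and date, never by effect on results.

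These changes concern eligibility wording, recording, follow-up and analysis. They leave the decision to change a drug with the clinicians. The cost is a wording amendment, a few data fields in both arms and one extra analysis. The small downside is that drug changes will add some noise to the primary comparison.

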**3.7.3 Strategies to improve adherence to interventions**

To promote adherence to the interventions, free measures (including vascular endothelial function testing, hemodynamic monitoring, the 6-minute walk test [6MWT], HRV testing, recording of symptoms, and scoring of depression and anxiety) will be offered following treatment.

**3.8 Guarantee of treatment adherence**

Since this study was completed during the patient's hospitalization, the patient's treatment compliance could be educated by the supervising physician about the patient's compliance.

**3.9 Outcomes**

**3.9.1 Primary outcome**

The primary outcome measures will focus on the levels of hsCRP and interleukin-6 in the peripheral serum following 20 cardiovascular ultrasound therapy sessions (i.e., on the 10th day). Comparative analyses will be conducted between the cardiovascular ultrasound therapy intervention and control groups along with pre- and postintervention assessments.

**3.9.2 Secondary outcome**

**(1) Indicators of serum myocardial injury and blood lipid levels**

Serum biomarkers indicative of myocardial injury encompass creatine kinase isoenzymes (CK-MB), cardiac troponin I (c-TnI), and myeloperoxidase (MPO). Lipid profile markers in serum comprise total cholesterol (TC), triglycerides (TG), low-density lipoprotein cholesterol (LDL-c), high-density lipoprotein cholesterol (HDL-c), apolipoprotein A (ApoA), apolipoprotein B (ApoB), lipoprotein (a), and oxidized low-density lipoprotein (ox-LDL) in the peripheral blood.

Monitoring of serum biomarkers indicative of myocardial injury will be conducted at baseline (24th hour post PCI), on the 10th day, and at the end of the 1st and 3rd months post intervention.

**(2) Serum markers of endothelial function**

The serum markers utilized to assess endothelial function encompass endothelial nitric oxide synthase (eNOS), endothelin-1 (ET-1), and vascular endothelial growth factor (VEGF) in the peripheral blood.

Monitoring of serum endothelial function will be conducted at baseline (24th hour post PCI); on the 5th and 10th days; and at the end of the 1st and 3rd months post intervention.

**(3) Serum inflammatory factors**

Each morning, 5 mL of fasting venous blood will be drawn by nursing staff to assess the proportion of inflammatory cells and measure levels of inflammatory markers in the peripheral blood.

Monitoring of serum inflammatory factors will be conducted at baseline (24th hour post PCI), on the 10th day, and at the end of the 1st and 3rd months post intervention.

**(4) Hemodynamic parameters**

These encompass a comprehensive range of indicators, including cardiac index (CI), cardiac output (CO), stroke volume (SV), stroke volume index (SVI), mean arterial pressure (MAP), stroke systemic vascular resistance index (SSVRI), left ventricular stroke work index (LVSWI), systemic vascular resistance index (SVRI), ejection phase contraction index (EPCI), inotropic state index (ISI), systemic vascular resistance (SVR), vascular resistance (VR), and mean heart rate (mHR).

Certified sonographers will monitor hemodynamic parameters at baseline (24th hour post PCI); on the 5th and 10th days; and at the end of the 1st and 3rd months post intervention.

**(5) Echocardiography**

The echocardiogram parameters will encompass E/e' ratio, left ventricular ejection fraction (LVEF), and wall thickening fraction (WTF). WTF is defined as [(end-diastolic wall thickness − end-systolic wall thickness)/ end-diastolic wall thickness] × 100 (%).

Echocardiographic assessments will be conducted by certified sonographers proficient in thoracic echocardiography. This will be done at multiple time points: at baseline (24th hour post PCI), on the 5th and 10th days, and at the end of the 1st and 3rd months post intervention.

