**3.4 Calculation of sample size**

Our calculations of sample size and power are based on the primary outcomes, utilizing a two-sided analysis with a statistical power of 90 % (1 – β = 0.90) and a significance level of α = 0.05. Owing to the lack of prior studies examining cardiovascular ultrasound therapy following PCI, the sample size was determined following an extensive evaluation by a panel of experts. Targeting long-term inflammation and cardiovascular efficacy, they selected high-sensitivity C-reactive protein (hsCRP) as the primary biomarker, given its relevance and the larger sample size required by interleukin 6.

Cardiovascular ultrasound is estimated to reduce hsCRP levels by an average of 4 mg/L. To meet this target, 160 participants (80 per group in a 1:1 allocation) are projected to be needed. Factoring in an anticipated dropout rate of 20 %, the final sample size would be adjusted to 200 participants (100 per group), ensuring adequate statistical power and robustness for the study’s objectives.

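### The wall thickening fraction formula has its numerator reversed, so a wall that thickens in systole scores negative (minor; one secondary outcome)

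*Protocol*

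**What the plan says.** Section 3.9.2 (5) of the protocol names three echocardiographic secondary outcomes: "The echocardiogram parameters will encompass E/e' ratio, left ventricular ejection fraction (LVEF), and wall thickening fraction (WTF"). It then gives the formula: "WTF is defined as [(end-diastolic wall thickness − end-systolic wall thickness)/ end-diastolic wall thickness] × 100" (%). The protocol summary, under Study outcomes, item 1.6, prints the same formula with the terms in the same order.

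WTF has no analysis rule of its own. It falls under the general provision of section 4: "Group comparisons will be conducted using independent sample tests, and within-group comparisons before and after treatment will be evaluated using paired sample tests". That section sets a 0.05 significance level. A two-sided analysis is stated only in section 3.4, for the sample size on the primary outcomes: "utilizing a two-sided analysis with a statistical power of 90 % (1 – β = 0.90) and a significance level of α = 0.05".

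The protocol nowhere takes the absolute value of WTF, reverses its sign, or says whether higher or lower values are favourable.

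**The concern.** A thickening fraction should measure how much the wall gains in thickness from end-diastole to end-systole, relative to its end-diastolic thickness. That requires the end-systolic value minus the end-diastolic value in the numerator. The protocol subtracts in the other order, so the formula contradicts the name of the quantity that it defines. Both statements of the formula agree, so no correct version elsewhere in the document can override the wrong one.

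What is at stake is the interpretation of this outcome. WTF is listed beside left ventricular ejection fraction, where a higher value is ordinarily taken to mean better contraction (the protocol states no direction for either measure). Applied literally, the printed formula makes the two measures move in opposite directions for the same improvement in contraction. A reader who takes higher WTF as better would then draw the wrong conclusion about whether the treatment helped or harmed.

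**Working it through.** **Inputs**

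- Printed formula (protocol summary, item 1.6, and section 3.9.2 (5)): WTF_printed = (D − S)/D × 100, where D is end-diastolic and S is end-systolic wall thickness.
- Formula implied by the name: WTF = (S − D)/D × 100.
- Wall thicknesses: the protocol gives none. Assumed for illustration only: D = 10 mm; S from 12 to 15 mm for a wall that thickens; S = 9 mm for one that thins.

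The protocol states no WTF value, so there is no figure of its own to reproduce.

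**Step 1: sign of the values**

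| D (mm) | S (mm) | Printed: (D − S)/D × 100 | Reversed order: (S − D)/D × 100 |
| --- | --- | --- | --- |
| 10 | 9 (thins) | +10% | −10% |
| 10 | 10 (no change) | 0% | 0% |
| 10 | 12 | −20% | +20% |
| 10 | 13 | −30% | +30% |
| 10 | 14 | −40% | +40% |
| 10 | 15 | −50% | +50% |

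The sign result does not depend on the assumed thicknesses. For any D > 0, the printed formula is positive only when S < D, that is, when the wall thins.

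**Step 2: sign of a change**

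Suppose S rises from 12 to 14 mm with D fixed at 10 mm, so that thickening increases.

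- Printed formula: −40 − (−20) = −20 percentage points.
- Reversed order: 40 − 20 = +20 percentage points.

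The size is the same and the direction is opposite.

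**Step 3: effect on the planned tests**

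For every participant, WTF_printed = −WTF. If all values carry the printed sign, group means and the difference between them change sign, while the standard deviations stay the same. The test statistic therefore changes sign only. As a check, a two-sample t-test was run on simulated data (assumed means 35 and 30, standard deviation 10, 80 per group) and then on the same data multiplied by −1:

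- original sign: t = 3.92, two-sided p = 0.00013;
- reversed sign: t = −3.92, two-sided p = 0.00013.

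**Step 4: reach of the error**

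Section 3.9.1 makes hsCRP and interleukin-6 on day 10 the primary outcomes. Section 3.4 bases the sample size on hsCRP. WTF enters neither.

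**The case against.** The strongest reply is that this is a slip in a definition with no inferential cost. WTF is one of many secondary measures. Used uniformly, the printed formula multiplies every value by −1, so no two-sided test result changes and the sign can be put right after data collection. Certified sonographers make the measurements, and a listing in which nearly every contracting wall has a negative thickening fraction would probably be noticed. All of this stands, and it is why the point is minor. It does not make the definition right: the sign of the reported difference is what tells a reader benefit from harm, and the protocol gives no rule for interpreting a negative value.

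A reader might infer two stronger things that the documents do not support.

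- **That an improvement will be reported as a worsening.** This needs the formula to be applied literally and higher values to be read as better. The name suggests that direction, but the protocol does not state it.
- **That pooled data will mix signs across hospitals,** with some using the conventional order and others the printed one. Mixed signs would do real damage, because opposite-signed values would dilute the pooled difference instead of merely turning it round. However, the protocol does not say whether WTF is computed at the site, by the machine or centrally, and nothing in it indicates that sites would differ. This is a possibility only.

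**Conclusion.** The definition is wrong as written, in both places where it appears. The finding is minor. Under literal and uniform use, every WTF value and every group difference has the wrong sign, for example −20% to −50% in place of +20% to +50% at the assumed thicknesses. The absolute size of the difference is unaffected. So is the p-value, provided that the tests on WTF are two-sided; the protocol says this only for the primary outcomes, and it is assumed here for WTF. Inversion of the apparent treatment effect relative to ejection fraction further assumes that higher is read as better for both measures. The primary outcomes, the sample size and the power are not touched.

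**What to change.** In the protocol summary (Study outcomes, item 1.6) and in section 3.9.2 (5), swap the two terms of the numerator, so that WTF = [(end-systolic − end-diastolic wall thickness) / end-diastolic wall thickness] × 100 (%). State that this one formula applies at all sites.

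The cost is one formula corrected in two places. It needs no new measurements and no change to the design or sample size. If any values have already been derived with the printed formula, multiplying them by −1 corrects them. Recording the two raw thicknesses and deriving WTF centrally would be a further safeguard. It is optional, and it may need extra case report fields if those thicknesses are not already collected.
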